**Fig. 2 Fig2:**
[figure not shown]
Example of EMI flow app for anger construct

The intervention of the CUIDA-TE app is grounded on 1) self-awareness of emotions through daily assessment and 2) learning and training adaptive responses depending on the nature and intensity of the emotion.

Shared features (the initial instructions and the assessment) from both apps also include an equivalent graphical user interface. Figure 3 shows an example of the graphical user interface of both apps. Both APPs have a missing alarm as well. If the user does not answer to the daily EMA during four consecutive days, the lead researcher will receive an automatic email warning and contact the user to check if they have a technical problem or if this reflects a potential dropout. This procedure aims to reduce attrition rates.

**Fig. 3 Fig3:**
[figure not shown]
Graphical User Interface example of both applications

### Randomization and procedure

Participants will be volunteers of a healthcare provider company (GESMED) and different healthcare organizations (online recruitment). For volunteers recruited online, the call of participants will be made using an open campaign that will be disseminated via social networks (WhatsApp, Instagram, Twitter, Facebook, and LinkedIn) and personal contacts. For the GESMED volunteers, the call of participants will be done sending an internal e-mail to the workers offering the study information and the website for the study (www.cuidateapp.com). Interested candidates from both sources who meet the inclusion criteria will be included in the study after the informed consent is signed online. The randomization will be conducted by an independent researcher not involved in the study and qualified from clinical point of view. Participants will be allocated to one of the three conditions using a computer-generated random software (Random allocation software 2.0 [101];). After signing the consent form and once the randomization is made, the participants will know the condition in which they are allocated and will receive a brief explanation of the characteristics of their condition.

First, all users will fill the baseline questionnaires (primary and secondary outcomes) online. The first intervention group will use the CUIDA-TE app during 2 months. The second intervention group will use MONITOR EMOCIONAL app, again during 2-months. The wait-list control group will remain without treatment in a waiting list condition during 2-months. After that, they will be offered the opportunity to receive the intervention app (CUIDA-TE app) if the interim analyses support this. Primary and secondary outcomes will be measured again at post-treatment (2 months after the baseline assessment) and at follow-up (3 months).

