## Methods/design

### Study aims and design

The goal of this study is to evaluate the efficacy of an ecological, momentary, and self-administered transdiagnostic psychological intervention via smartphone for healthcare professionals (compared to an ecological momentary assessment group and a wait-list group) to decrease depression, difficulties in emotion regulation and increase professional quality of life and resilience. We also would like to study the usability and acceptability of the technology.

The current study will use a randomized controlled superiority trial design. A minimum of 174 healthcare workers will be randomly assigned into three conditions: (1) EMI intervention group, (2) EMA intervention group, and (3) wait-list control group. An online informed consent form will be signed by the participants before randomization. Assessments will be conducted at pre-treatment, post-treatment, and 3- month follow-up. The experimental groups will use different apps during 2 months: the experimental group (1) will use an EMI app (CUIDA-TE) and the experimental group (2) will use an EMA app (MONITOR EMOCIONAL). For ethical reasons, when the wait-list group completes the post-treatment assessment (2 months after the base-line evaluation), the EMI app will be offered if the interim analyses support this. Participants in the EMA condition will also be offered this option at the end of the 3-month follow-up, again if the results support this. The trial has been approved by the Ethics Committee of Humans Research of the Ethics Commission in Experimental Research of University of Valencia (Spain) and it has been registered in clinicaltrials.gov as NCT04958941 (https://clinicaltrials.gov/ct2/show/NCT04958941). The study will adhere to the recommendations of the Consolidated Standards of Reporting Trials (CONSORT) [67]. The design of the study is outlined in Fig. 1.

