### Measures description

#### Primary and secondary outcomes

The sociodemographic information (see Supplementary file 1) will be gathered with an ad hoc questionnaire that evaluates sex, age, specific healthcare profession, marital status, if they share their home with a COVID-19 vulnerable person, where they work (type of health care center, such us hospital, primary care, nurse home, etc.), if they work directly with COVID-19 patients, and number of COVID-19 deaths in their region (this will be collected from external, official sources) [2].

The primary outcome is the Brief Patient Health Questionnaire Mood Scale (PHQ-9) for depression. Secondary outcomes include the Emotion Regulation Questionnaire (ERQ), the Difficulties in Emotion Regulation Questionnaire (DERS), the Brief Resilience Scale (BRS), and the Short Professional Quality of Life Scale (ProQOL Short). Primary and secondary outcomes will be obtained at baseline, post-intervention, and 3-month follow-up.

The PHQ-9 is a 9-item depression module from the full PHQ where the user indicates the severity of depression during the previous 2 weeks. The symptom is presented in a scale measuring the frequency from 0 to 3 (0= “not at all” to 3 =” nearly every day”). The PHQ-9 has demonstrated its validity as a brief measure of depression severity in clinical samples [71] and the general population [72]. The PHQ-9 score is divided into the following severity categories: 5–9 (mild depression), 10–14 (moderate depression), 15–19 (moderately severe depression), and 20 or greater (severe depression). The range for the PHQ-9 is 0-to-27. The Spanish version of the scale has demonstrated good psychometric properties [73].

The ERQ is a 10-item self-report measure that evaluates the use of cognitive reappraisal and emotion suppression as ER efforts to regulate emotions [74, 75]. The items are rated on a 7-point scale (1 = “strongly disagree” to 7 = “strongly agree”). We will use the Spanish adaptation of the ERQ [76], which has obtained good internal reliability estimates for both reappraisal (.79) and suppression (.75).

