## Data analysis plan

First, to ensure that the randomization process was successful, the three study conditions will be compared at baseline on all study outcomes. Then, a multilevel linear mixed model, which effectively handles missing data, will be computed. All assessment points will be included in the model. A restricted maximum likelihood method will be used to estimate the parameters. If differences at baseline are revealed, we will include them as covariates in the linear mixed model. Effect sizes (Cohen’s d) will be calculated [103]. Usability and acceptability will be evaluated with descriptive analyses.

All analyzes will be performed with SPSS v26.0. To conduct and report the study, we will follow the recommendations of the Consolidated Standards of Reporting Trials (CONSORT) [67].

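### The baseline PHQ-9 is written as completed after participants learn their arm, which can bias the primary contrast

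*Protocol article*

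**What the plan says.** The order of events is given in Randomization and procedure. Eligible volunteers consent online, an independent researcher allocates them by software, and then: "once the randomization is made, the participants will know the condition in which they are allocated". At that point they also "will receive a brief explanation of the characteristics of their condition". The next paragraph begins: "First, all users will fill the baseline questionnaires (primary and secondary outcomes) online". App use or waiting follows directly.

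Study aims and design fixes one thing relative to allocation: "An online informed consent form will be signed by the participants before randomization". It does not place the baseline assessment there. Elsewhere the measurement is called baseline, pre-treatment or pre-intervention, never pre-randomisation.

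On the outcome, the section on primary and secondary outcomes states: "The primary outcome is the Brief Patient Health Questionnaire Mood Scale (PHQ-9) for depression". It is a self-report in which "the user indicates the severity of depression during the previous 2 weeks".

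The Data analysis plan gives baseline three jobs. It serves as a check: "to ensure that the randomization process was successful, the three study conditions will be compared at baseline on all study outcomes". It is one of the assessment points in the linear mixed model. Any baseline difference that is found is to be added as a covariate.

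**The concern.** All three uses of baseline presuppose a measurement that allocation cannot have influenced. In the written sequence, participants report their mood just after being told that they will receive an intervention app, a monitoring app or nothing for two months. Disappointment, relief or expectation can colour the answers to PHQ-9 and to the secondary scales (DERS, ERQ, BRS, ProQOL), which are also self-reported.

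Two things are at stake. First, an arm-specific shift in baseline passes into the between-arm comparison of change. Second, a participant unhappy with the wait-list can leave before giving any baseline, so the people who supply data may differ between arms in a way that randomisation no longer protects. The baseline comparison cannot detect either problem cleanly, because a difference could come from chance, from a fault in allocation, from a reaction to disclosure, or from selective departure.

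**Working it through.** **1. The order of events.** Side by side, the text gives: consent (before randomisation, in both sections); randomisation; disclosure with an explanation of the arm; baseline questionnaires; app or waiting. No sentence in the article puts baseline earlier.

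**2. The plan's own figure, to see which contrast the trial was sized for.** Inputs from Sample size: effect size 0.20, alpha 0.05, power 80%, k = 3 groups, m = 3 measurements. For a group-by-time interaction take df1 = (k − 1)(m − 1) = 4, df2 = (N − k)(m − 1) and noncentrality f²·N·(m − 1). The smallest N reaching 80% power is 152, with noncentrality 0.04 × 152 × 2 = 12.16. This equals the stated 152. Other conventions give different numbers (for example 164 for the between-groups test at correlation 0.5). The match therefore points to group-by-time, the contrast that uses baseline directly, although the article does not name it.

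**3. How a baseline shift enters the estimate.** Let disclosure shift one arm's baseline by b SD, with no such shift at post-test, and let ρ be the baseline–post correlation.
- Difference in change = (post difference) − (baseline difference), so it moves by −b.
- In an analysis of later scores adjusted for baseline, it moves by about −ρb.

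**4. Size.** The documents give neither b nor ρ. Assumed: b = 0.1 to 0.2 SD, ρ = 0.5 to 0.7, no true effect, and n = 50 analysed per arm (58 × 0.85 = 49.3; 152/3 = 50.7). Standard errors in SD units:
- change: √(4(1 − ρ)/n) = 0.200 at ρ = 0.5 and 0.155 at ρ = 0.7;
- baseline-adjusted: √(2(1 − ρ²)/n) = 0.173 and 0.143.

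With z = |bias|/SE, the two-sided rejection rate is 1 − Φ(1.96 − z) + Φ(−1.96 − z). Example: b = 0.2 and ρ = 0.5 for change give z = 0.2/0.200 = 1, hence 17.0%.

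| b (SD) | ρ | Bias, change | Type I error, change | Bias, adjusted | Type I error, adjusted |
|---|---|---|---|---|---|
| 0.1 | 0.5 | 0.10 | 7.9% | 0.05 | 6.0% |
| 0.1 | 0.7 | 0.10 | 9.9% | 0.07 | 7.8% |
| 0.2 | 0.5 | 0.20 | 17.0% | 0.10 | 8.9% |
| 0.2 | 0.7 | 0.20 | 25.2% | 0.14 | 16.5% |

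The nominal rate is 5%. Baseline adjustment reduces the bias but does not remove it.

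**5. Loss before baseline.** A mixed model can use someone who misses baseline but answers later. It has nothing to use from someone who leaves at disclosure and does not return. The documents give no rate for this, so no size can be attached.

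**The case against.** The strongest reply is that the order is inferred from the sequence of two paragraphs. The second opens with a word that could mark the first step of taking part rather than the step after disclosure. The design flowchart (Fig. 1) might show baseline before allocation and was not available here. Using baseline to check randomisation also suggests that the authors think of it as untouched by allocation. This is fair as a statement about intent. It does not rescue the text: if baseline is meant to come first, the procedure section describes the wrong sequence and needs the same correction.

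A second reply concerns mechanism. The one-for-one bias requires the shift to be absent at post-test, yet participants remain unblinded throughout. If a fraction p of the shift persists, the change contrast moves by −(1 − p)b and the adjusted one by (p − ρ)b. With full persistence the change contrast is undisturbed, while the adjusted one still moves by (1 − ρ)b, or 0.03 to 0.10 SD over the ranges used above. The two-week recall window of PHQ-9 may also dampen an immediate reaction. Both points stand: the bias may be smaller than tabulated, and its sign is unknown. Neither makes a post-disclosure baseline a sound one.

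Third, the 0.1 to 0.2 SD is assumed, and the selection argument applies only to those who never return. Both limits are accepted.

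**Conclusion.** The concern holds. Followed as written, the plan takes its baseline, including the primary outcome, after participants know their arm, and then treats that baseline as a pre-allocation measure. This can bias the primary contrast; it need not. For a disclosure shift of 0.1 to 0.2 SD that is absent at post-test, the bias is 0.1 to 0.2 SD in the change contrast and 0.05 to 0.14 SD after baseline adjustment. At about 50 per arm the corresponding type I error is 7.9% to 25.2% and 6.0% to 16.5%. These sizes rest on assumed values of the shift and the correlation. The fault in the stated order does not. It should be corrected before enrolment, because analysis cannot fully repair it afterwards.

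**What to change.** Set the online workflow to: consent, completed baseline questionnaires, randomisation, disclosure of the arm and issue of the app code. Randomise only people whose baseline has been submitted, so that the independent researcher who runs the allocation software receives only their IDs. State this order in Study aims and design and in Randomization and procedure, and check that Fig. 1 agrees. If this is already the intended order, only the text needs correcting.

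The cost is a reordering of web forms, the matching hand-off to the allocating researcher, and two sentences of protocol text. The article reports that recruitment has not started, so no extra participants or assessments are needed. The change protects the baseline and ensures that every randomised participant has one. It does not remove open-label reporting bias at post-test, which any unblinded trial with a self-reported outcome retains.

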## Ethics and dissemination

This study follows the ethical standards of the Declaration Helsinki and existing guidelines of Spain and the European Union for humans’ protection in clinical trials. All participants will be volunteers, and once the study has been explained to them and if they agree to participate, they will sign an online informed consent form. Participants will be able to withdraw from the study at any time. Regarding data security, both apps will follow the strictest rules, namely the General Data Protection Regulation (GDPR), Organic Law 3/2018 of 5 December and regulation 2016/679 of the European Parliament and of the Council [102] and neither CUIDA-TE nor MONITOR EMOCIONAL will store any personal data. The data will be stored on two servers connected locally at the University, following the corresponding legal regulations. However, the APP will not collect any personal data. The users will be identified with an external anonymous ID provided by the researcher. This information will only be known by the user and the lead researcher. This project, entitled “CUIDA-TE, an APP for the emotional management of the healthcare professionals” was approved by the Ethics Commission in Experimental Research of the University of Valencia in May 2021 (Register code: 1547727). It has been registered in clinicaltrials.gov (https://clinicaltrials.gov) as NCT04958941 (https://clinicaltrials.gov/ct2/show/NCT04958941).

## Data analysis plan

First, to ensure that the randomization process was successful, the three study conditions will be compared at baseline on all study outcomes. Then, a multilevel linear mixed model, which effectively handles missing data, will be computed. All assessment points will be included in the model. A restricted maximum likelihood method will be used to estimate the parameters. If differences at baseline are revealed, we will include them as covariates in the linear mixed model. Effect sizes (Cohen’s d) will be calculated [103]. Usability and acceptability will be evaluated with descriptive analyses.

All analyzes will be performed with SPSS v26.0. To conduct and report the study, we will follow the recommendations of the Consolidated Standards of Reporting Trials (CONSORT) [67].

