**Methods:**

In this three-arm, randomized controlled trial (RCT) the study sample will be composed of a minimum of 174 healthcare workers. They will be randomly assigned to a 2-month EMI group (CUIDA-TE APP, *n* ≥ 58), a 2-month ecological momentary assessment (EMA) only group (MONITOR EMOCIONAL APP, n ≥ 58), or a wait-list control group (no daily monitoring nor intervention, n ≥ 58). CUIDA-TE will provide EMI if EMA reveals emotional problems, poor sleep quality/quantity, burnout, stress, or low perceived self-efficacy when regulating emotions. Depression will be the primary outcome. Secondary outcomes will include emotion regulation, quality of life, and resilience. Treatment acceptance and usability will also be measured. Primary and secondary outcomes will be obtained at pre- and post-intervention measurements, and at the 3-month follow-up for all groups.

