The EMI will be an interactive intervention allowing healthcare workers to record their emotional states at momentary periods. In addition, they will receive contextual ER strategies on request. Considering the recent research on ER strategy choice [49, 53, 66], the logic of displaying one ER strategy or another via EMI will be based on the type of emotional state and emotional intensity reported by the participant. On the other hand, because emotional awareness is a form of emotion regulation processing [66], assessing emotions daily may help improve the self-awareness of emotions, thus contributing to a better emotional regulation. Therefore, an EMA only condition will be included in this study to distinguish the effect of EMA and EMI. The EMI protocol will include different transdiagnostic cognitive behavioral interventions that will be administered to healthcare workers who are or have been recently and repeatedly exposed to COVID-19 related stress. The treatment will be administered via smartphone during 2 months. Treatment efficacy will be evaluated at post-treatment and 3 months later (follow-up). To the best of our knowledge, this is the first investigation that aims to evaluate the efficacy of an ecological, momentary, and self-administered transdiagnostic psychological intervention via smartphone for healthcare professionals during the pandemic.

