### Sample size

The sample size was calculated a priori using GPower [68]. Assuming a conservative effect size of 0.20, an alpha level of 0.05, an 80% power, three groups, and 3 measurements, a sample of 152 was obtained. Assuming a 15% of attrition, we will recruit a minimum of 174 participants. The small attrition rate is based on a systematic review showing that interventions for mental health that incorporate technology, such as blended interventions, tend to obtain lower dropout rates [69]. The effect size in favor of EMI compared to EMA and the control condition is also inspired by past research [70].

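### If the wait-list is offered CUIDA-TE after month 2, its follow-up is no longer untreated-control data, yet the planned model takes it in without distinction

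*Protocol article*

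**What the plan says.** All references are to the protocol article.

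- **Wait-list access.** Under Study aims and design, once the wait-list has completed its post-treatment assessment at 2 months, "the EMI app will be offered if the interim analyses support this". Randomization and procedure repeats this: "After that, they will be offered the opportunity to receive the intervention app (CUIDA-TE app) if the interim analyses support this".
- **EMA access.** "Participants in the EMA condition will also be offered this option at the end of the 3-month follow-up", again conditional on results. The EMA arm therefore stays as randomised through follow-up.
- **Measurement.** The abstract's Methods paragraph says "Primary and secondary outcomes will be obtained at pre- and post-intervention measurements, and at the 3-month follow-up for all groups".
- **Efficacy time points.** The current study treatment says "Treatment efficacy will be evaluated at post-treatment and 3 months later (follow-up").
- **Analysis.** The Data analysis plan says "a multilevel linear mixed model, which effectively handles missing data, will be computed", and then "All assessment points will be included in the model". It makes no separate provision for wait-list follow-up values obtained after app access.
- **Sample size.** "Assuming a conservative effect size of 0.20, an alpha level of 0.05, an 80% power, three groups, and 3 measurements" gives 152, raised to a minimum of 174 for 15% attrition.

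**The concern.** The wait-list is a no-treatment control only up to month 2. If the offer is made, its follow-up values come from a mixture of people who have and have not used the EMI app. The plan evaluates efficacy at that wave and enters it in the model for every arm, without saying what the wait-list represents there.

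Two results are at stake. The follow-up difference between EMI and wait-list shrinks as switchers benefit, so a lasting effect could be reported as having faded. A test of any group-by-time difference over three waves also picks up the wait-list's late improvement, so a significant result would not by itself mean that EMI did better than an untreated control. The offer depends on supportive interim results, so the problem is most likely to arise when the app appears to work.

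**Working it through.** **1. Timing.** The current study treatment puts follow-up 3 months after post-treatment, which is month 2 + 3 = month 5. A wait-list participant who starts the 2-month app at month 2 could finish at month 4. Randomization and procedure says only that follow-up is at 3 months, which could be read as month 3, one month into the course. On either reading, follow-up comes after the offer.

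**2. Which test gives 152?** The article does not name the powered test. For a group-by-time interaction with k = 3 groups, m = 3 waves and f = 0.20 on Cohen's scale:

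- λ = f² × N × (m − 1), df1 = (k − 1)(m − 1) = 4, df2 = (N − 3) × 2.
- N = 151: λ = 0.04 × 151 × 2 = 12.08, power 0.798.
- N = 152: λ = 12.16, power 0.801.

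So 152 is exactly the smallest N that reaches 80%. Other standard variants at f = 0.20 give 53 (interaction, default effect-size convention, correlation 0.5), 164 (between-groups, correlation 0.5) and 244 (one-way). The powered test therefore appears to be a three-wave interaction that includes follow-up. This is an inference.

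**3. Dilution at follow-up.** Assumptions, none of them in the article:

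- 50 per arm (152 / 3 ≈ 50.7);
- EMI effect 0.53 SD at both post-treatment and follow-up;
- EMA equal to an untreated wait-list;
- correlation 0.5 between waves;
- a fraction u of the wait-list takes the app and gains the full effect.

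The expected EMI minus wait-list difference at follow-up is 0.53 × (1 − u). Two-sided power at 5% comes from a noncentral t with noncentrality difference × √(50/2) and 98 df.

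**4. The three-wave test.** Each arm's mean changes are (post − baseline, follow-up − baseline): EMI (0.53, 0.53), EMA (0, 0), wait-list (0, 0.53u). Their covariance is S = (1 − 0.5) × [[2, 1], [1, 2]] = [[1, 0.5], [0.5, 1]]. With B the between-arm matrix of these means (average over the three arms), V = tr[B(B + S)⁻¹], f² = V / (2 − V), λ = 2 × 150 × f², df 4 and 294.

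| Uptake u | Follow-up difference (SD) | Power, EMI vs wait-list at follow-up | λ, three-wave test | Power, three-wave test |
|---|---|---|---|---|
| 0% | 0.53 | 75% | 11.99 | 79% |
| 25% | 0.40 | 50% | 11.34 | 77% |
| 50% | 0.27 | 26% | 12.27 | 81% |
| 75% | 0.13 | 10% | 14.75 | 88% |
| 100% | 0 | 5% (alpha) | 18.73 | 95% |

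The pairwise contrast weakens steadily. The omnibus test barely moves up to 50% uptake and then gains power, because the treated wait-list departs from EMA.

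**5. Sample size if wait-list comparisons use two waves.** On the convention that reproduces 152, with m = 2: λ = 0.04 × 152 = 6.08, df 2 and 149, power 0.58. Reaching 80% needs N = 244, or 244 / 0.85 = 287.1, so 288 with 15% attrition. On the default convention with an assumed correlation of 0.5, λ = f² × N × m / (1 − 0.5), the two-wave test needs only 64, and 152 is ample (power above 0.99). The answer depends on which convention the 0.20 was meant on.

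**The case against.** The strongest defence is that the article never says switched wait-list data will be read as untreated. It names no group-by-time term and no follow-up contrast, and the offer may never be made. EMI versus wait-list at follow-up is also a valid randomised comparison of immediate with delayed access. These points stand, and they limit the problem to an untreated-control reading of follow-up. They do not remove it: the article evaluates efficacy at follow-up, puts that wave in the model for all arms, and nowhere declares the immediate-versus-delayed reading.

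Uptake and full catch-up are also assumed. If follow-up is at month 3, switchers would have had at most half the course, and dilution would probably be smaller than in the table.

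A reader might infer three stronger things that the documents do not support:

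- **That all the comparisons are compromised.** Month-2 contrasts precede any switch and, with time treated as categorical, modelling a later wave does not bias them. EMA is offered the app only after follow-up, so EMI versus EMA holds there too.
- **That switching follows unblinded results seen by those running the trial.** The article says only interim analyses. It does not say who sees them, when, or how often, and those details may sit in a fuller document.
- **That the omnibus test would often be falsely positive with an ineffective app.** This needs an app that does nothing in the EMI arm yet helps the wait-list, and it overlooks that the offer requires supportive interim results.

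**Conclusion.** The point holds in this limited form. If the offer is made, the plan as written yields a follow-up comparison with the wait-list that cannot be read as EMI against no treatment, and a three-wave omnibus test that partly reflects treated controls. The direction of the dilution requires only that some wait-list participants take the app and benefit from it. The sizes rest on the assumptions above: at 50% uptake the contrast halves and its power falls from 75% to 26%, while omnibus power changes little until uptake is high. That the omnibus test is the powered one is inferred from the exact reproduction of 152. This should be settled before recruitment starts, because an efficacy time point and the apparent basis of the sample size are both affected.

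**What to change.** 1. State that efficacy comparisons with the wait-list are made at post-treatment (month 2).
2. Use follow-up for EMI versus EMA as the controlled comparison.
3. Leave wait-list follow-up out of any untreated-control contrast and out of the omnibus test. Report it descriptively by app uptake, or label it explicitly as immediate versus delayed access. Align the abstract and aims.
4. Restate the sample-size basis for the retained contrast and say which effect-size convention the 0.20 uses.
5. Reconcile the interim-analyses clause in Study aims and design and in Randomization and procedure with the Data analysis plan. The access rule itself is for the sponsor to decide.

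Most of this is wording, and recruitment had not started. There are two real costs. The trial gives up a controlled follow-up claim against an untreated wait-list, which it cannot support once the app has been offered. The sample-size check may also show that 152 is too few on the convention that reproduces it.

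### Baseline adjustment depends on observed differences, and with baseline already a response, a main-effect covariate would neither correct a chance imbalance nor gain precision

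*Protocol article*

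**What the plan says.** The Data analysis plan begins with a check on the allocation: "to ensure that the randomization process was successful, the three study conditions will be compared at baseline on all study outcomes". A linear mixed model follows. On its responses the plan says "All assessment points will be included in the model", and on estimation, "A restricted maximum likelihood method will be used to estimate the parameters". The covariate rule is "If differences at baseline are revealed, we will include them as covariates in the linear mixed model".

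Study aims and design lists the assessment points: "Assessments will be conducted at pre-treatment, post-treatment, and 3- month follow-up". The subsection Primary and secondary outcomes confirms that PHQ-9 and all secondary scales are measured each time: "Primary and secondary outcomes will be obtained at baseline, post-intervention, and 3-month follow-up". Pre-treatment is therefore an assessment point, and the baseline score is a response in the model.

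The section does not name the contrast that carries the treatment effect. It does not say whether a covariate enters alone or with a covariate-by-time term, and it sets no threshold for a difference. No covariate is fixed in advance.

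**The concern.** The rule has two parts, and neither does its job.

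First, the arms are compared on the outcomes at baseline to see whether randomisation succeeded. Under sound randomisation every baseline difference is due to chance, so such a comparison cannot answer that question.

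Second, the remedy for an observed difference is to add the differing variable as a covariate. In a model that already has baseline among its responses, a covariate that is constant within a participant shifts all of that participant's time points equally. It therefore drops out of any comparison of change between arms. A chance PHQ-9 imbalance would stay in the estimate through regression to the mean, while the report would say that it had been adjusted for. When no difference is found, the baseline score is not used as a covariate at all, and the precision it offers is given up.

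**Working it through.** **Inputs from the protocol.** Three arms of at least 58; three assessment points; REML mixed model; 15% attrition; five instruments as primary and secondary outcomes (PHQ-9, ERQ, DERS, BRS, ProQOL Short).

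**Assumptions, not in the protocol.** Outcome SD 5; equal correlation ρ between time points, 0.5 unless a range is shown; a 0.05 level for baseline tests; independence of those tests.

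**Which contrast is meant.** The sample size inputs are "Assuming a conservative effect size of 0.20, an alpha level of 0.05, an 80% power, three groups, and 3 measurements". A group-by-time test with numerator df (3−1)(3−1) = 4 and noncentrality f²·N·(m−1) = 0.04 × 152 × 2 = 12.16 reproduces the stated 152. This fits a group-by-time analysis but does not prove one: a between-arm test with ρ of about 0.42 to 0.44 gives 151 to 154.

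**1. Cancellation.** Let ȳ(g,t) be the mean of arm g at time t, x̄(g) the arm mean of the covariate and γ its coefficient. With complete data and a main-effect covariate, the adjusted cell mean is ȳ(g,t) − γ·x̄(g), plus a constant. The change in arm g is

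[ȳ(g,1) − γ·x̄(g)] − [ȳ(g,0) − γ·x̄(g)] = ȳ(g,1) − ȳ(g,0).

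γ disappears whatever the SD or correlation, and whether the covariate is baseline PHQ-9 or another variable.

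REML random-intercept fits to one simulated trial (58 per arm, complete data, 2.5-point baseline shift in one arm) gave:

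| Model | Estimate | SE |
|---|---|---|
| No covariate | −2.66883 | 0.82508 |
| Baseline PHQ-9, main effect | −2.66883 | 0.82508 |
| Another covariate, main effect | −2.66883 | 0.82508 |
| Baseline × time | −1.33607 | 0.76643 |
| Post score adjusted for baseline (ANCOVA) | −1.33607 | 0.68039 |

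**2. Conditional bias.** With no true effect and a chance imbalance d, the expected change contrast is −(1−ρ)d. For an assumed d of 2.5 points (0.5 SD) and ρ = 0.5 this is −0.5 × 2.5 = −1.25. Means over 150 simulated trials were:

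| Data | No covariate | Baseline main effect | ANCOVA |
|---|---|---|---|
| Complete | −1.189 | −1.189 | 0.024 |
| 15% random dropout | −1.161 | −1.155 | 0.061 |

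With dropout (both later assessments lost) the cancellation is no longer exact. Single-trial estimates moved by up to 0.32 points (0.32/5 = 0.06 SD), but there was no correction on average. The reported SE fell from 0.990 to 0.954, while the actual spread of the estimates did not (0.970 without the covariate, 0.982 with it). The apparent gain in precision was not real.

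**3. Precision given up.** Per arm mean, the change score has variance proportional to 2(1−ρ) and the baseline-adjusted score to 1−ρ². The ratio is (1+ρ)/2.

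| Assumed ρ | Ratio | Variance cut | Equivalent sample size factor (1/ratio) |
|---|---|---|---|
| 0.3 | 0.65 | 35% | 1.54 |
| 0.5 | 0.75 | 25% | 1.33 |
| 0.7 | 0.85 | 15% | 1.18 |
| 0.8 | 0.90 | 10% | 1.11 |

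These figures rest on the formula; 150 simulated trials are too few to measure the gain.

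**4. The baseline check.** With five independent tests at 0.05, the chance of at least one significant difference under correct randomisation is 1 − 0.95⁵ = 0.226. The scales are related self-reports, so the true figure is probably lower.

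**The case against.** **The model is not fully described.** The section names neither the group-by-time contrast nor a main-effect-only covariate, and a journal article may leave the fixed effects to a fuller document. This stands as a limit. A covariate-by-time term would correct the imbalance, as the table shows, and a group effect averaged over all times would change with the covariate. The conditional rule itself, however, is stated outright and is not a gap left for later. With a covariate-by-time term the rule would still be poor, because the estimate would then depend on whether a difference happened to be revealed.

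**Data-driven selection distorts the result.** A reader might infer that the primary estimate hangs on arbitrary baseline p-values. On the main-effect reading it does not: a covariate that cannot move the contrast cannot distort it. The two criticisms cannot both apply to the same estimate, and the protocol gives no p-value threshold.

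**The analysis is biased.** A reader might also infer an invalid primary analysis. Over repeated randomisations the change contrast is unbiased. The −1.19 is conditional on an assumed 0.5 SD imbalance.

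**Adjustment may not be free of risk here.** Randomization and procedure has participants learn their condition once randomised, and then describes completion of the baseline questionnaires. If that is the true order, baseline self-report could be affected by knowledge of allocation. A stable arm difference d arising that way would leave a bias of about (1−ρ)d in a baseline-adjusted analysis and none in the change contrast; a shift confined to baseline reporting would favour adjustment. This stands and qualifies the fix.

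**Conclusion.** The point holds in a limited form. The protocol makes baseline adjustment conditional on observed differences, in a model where baseline is a response. With a main-effect covariate, the rule does nothing for the group-by-time contrast with complete data and next to nothing with 15% random dropout. The price is conditional bias of about (1−ρ) times any chance imbalance, and a variance that adjustment would cut by between 10% and 35% over assumed correlations from 0.8 down to 0.3. A saving equal to one-third more participants applies only at an assumed correlation of 0.5 and should not be quoted alone.

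The algebraic cancellation needs no assumed SD or correlation, but it does need complete data and the main-effect reading. The baseline comparison cannot certify the randomisation, and would raise a false flag in about 23% of trials under the stated assumptions. This is a should-fix matter of efficiency and prespecification. The documents do not support calling the primary analysis invalid.

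**What to change.** Delete the baseline comparison as a check on randomisation, and delete the conditional covariate rule. Show baseline values by arm descriptively.

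For every outcome, prespecify adjustment for its own baseline whatever the observed differences. Take post-treatment and 3-month follow-up as the responses, with arm, time, arm-by-time, baseline and baseline-by-time as fixed effects, and name the contrast that carries the treatment effect.

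State in Randomization and procedure whether baseline is completed before participants learn their allocation. Any baseline adjustment assumes that baseline is unaffected by that knowledge. A constrained longitudinal model, with all three times as responses and a common baseline mean across arms, is an alternative only if baseline comes first.

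The analysis change is one of wording. It needs no new data and runs in the same SPSS mixed procedure. Its one cost is that participants with neither later assessment do not contribute to the model. In the simulations with 15% dropout and the 2.5-point imbalance, the adjusted analysis still had the smaller mean model SE (0.899 against 0.990). If the present text does describe the true order, completing baseline before disclosure would be a change of procedure; recruitment is reported as not yet started.
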